## Abstract

Habitual physical activity and exercise training (PA/EX) confers numerous health-benefits. Phenotypic adaptations and clinical health outcomes attributable to PA/EX are well-established, and molecular markers and mediators of the PA/EX response have been described. To date, the majority of prior work focused on the biochemical response to PA/EX has leveraged convenience samples of trained athletes participating in events, patients undergoing clinically indicated exercise stress testing, or laboratory protocols comprised of a single dose of exercise. Accordingly, the impact of “exercise dose”, defined by the product of intensity, duration, modality, and frequency, on the human biochemical response to PA/EX remains largely unexplored. The Human Exersome Initiative (HEI) was designed to fill this scientific knowledge gap. Specifically, the HEI will couple carefully controlled laboratory-based acute exercise testing with comprehensive systemic biochemical profiling to isolate the impact of PA/EX duration and intensity on human biochemistry. Herein, we describe the initial phase of the HEI which will aim to comprehensively define the impact of “exercise dose” on blood-based biochemistry in healthy young men and women. The overarching goal of the HEI is to elucidate how the human exercise response varies as a function of phenotypic variability. Using comparator data derived from young men and women, future iterations of this protocol will seek to determine how key sources of human variability (i.e., age, ethnicity, and the presence of comorbid disease) impact the biochemical response to PA/EX. We anticipate results from this work will facilitate biomarker discovery, the elucidation of molecular pathways and mechanisms associated with metabolic responses to exercise, and the identification of optimal exercise doses for future clinical interventions (i.e., tailoring preventive and therapeutic strategies).

## Introduction

The health benefits attributed to habitual physical activity and/or structured exercise (PA/EX) have been well documented. Numerous classic epidemiologic datasets have established a direct, curvilinear relationship between PA/EX and all-cause mortality, with the largest risk reduction occurring at the lowest end of the exercise dose spectrum [1]. Consequently, the steepest reductions along the mortality risk curve occur between sedentary people and those performing relatively low levels of PA/EX. Careful analysis of these classic epidemiologic datasets underlie contemporary physical activity guidelines. Current recommendations suggest at least 150 weekly minutes of moderate intensity (i.e., 3–6 metabolic equivalents, METs) exercise or 75 weekly minutes of vigorous intensity (i.e., > 6 METs) exercise as these values correspond to the nadir (i.e., the initial flattening) of the PA/EX-mortality curve [2–4].

The benefits of PA/EX extend beyond reductions in mortality risk. Several randomized controlled trials document positive disease-specific outcomes in response to PA/EX [5–8]. In addition, habitual PA/EX stimulates organ system-specific adaptations including enhanced cardiovascular reserve (i.e., increased maximal cardiac output and lower blood pressure) [9], favorable skeletal muscle morphology adaptations (i.e., higher mitochondrial content, mitochondrial function, and capillarization) [10–12], and lower levels of chronic systemic inflammation [13]. While these phenotypic responses to PA/EX have been firmly established, the molecular markers and mediators of these adaptions remain incompletely understood [14–16].

Prior work examining the acute molecular responses of PA/EX have largely leveraged convenience samples. Athletes participating in endurance sport competitions [17–21], and clinical populations undergoing clinically indicated exercise testing during routine medical care [20], have been used to identify biochemical pathways and individual molecules that respond to PA/EX. In addition, a small number of studies have examined organ-specific and/or systemic biochemical changes in response to a single dose of PA/EX [22–27]. At present, a large US-based, federally-funded, multi-center consortium is examining the molecular mechanisms of an exercise training intervention [15]. Specifically, the Molecular Transducer of Physical Activity Consortium (MoTrPAC) aims to provide comprehensive biochemical profile of the response to steady-state sub-maximal exercise [65% of peak oxygen consumption (V̇O_2peak_)] before and after a 12-week training intervention [16]. In aggregate, prior and ongoing work has and will continue to identify molecular families and individual molecules that are either up-regulated or down-regulated by PA/EX. However, the potential importance of “exercise dose” on biochemical regulation and corollary clinical outcomes remains largely unexplored.

“Exercise dose” is defined by the product of intensity, duration, and frequency. This framework mirrors the principal components of pharmaceutical dosing: drug potency, frequency of administration, and duration of therapy. The ability to effectively tailor pharmaceutical prescriptions at the individual patient level is enabled by the carefully scripted scientific sequence of drug development which relies on pre-clinical studies to elucidate mechanisms of action and phase I clinical trials to establish dose-response relationships and safety, while phase II and III clinical studies determine mechanisms of action and effectiveness across diverse populations. Analogous to classical Phase I clinical studies, comprehensive laboratory-based work characterizing dose-response relationships between multiple acute bouts of PA/EX and blood-based biochemical profiles are lacking. The Human Exersome Initiative (HEI) was designed to fill this scientific knowledge gap. Specifically, the HEI will couple carefully controlled laboratory-based exercise testing of variable intensities, durations, and modalities with comprehensive systemic biochemical profiling (i.e., proteomic, metabolomic, lipidomic, transcriptomic) to probe the impact of exercise dose on human biochemistry.

## Methods

### Study design

The HEI is a prospective, longitudinal, repeated-measures, human participants study examining the biochemical response to variable doses of acute exercise bouts. Participants will perform 10 experimental exercise sessions at pre-determined exercise doses as defined by individualized relative intensities and fixed absolute durations. Peripheral venous blood samples will be collected before (baseline), immediately after (post), and 60 min after (recovery) exercise completion for all sessions. Participant recruitment and data collection for the first phase of the HEI began on October 2^nd^, 2024 and is anticipated to reach completion by July 15^st^, 2025. Results from the biochemical analyses described below are anticipated to be available by the end of 2025. All participants will provide oral and written consent at the time of enrollment. All study procedures described below adhere to the Declaration of Helsinki and have been approved by the local institutional review board (CER-VD 2024-00525).

### Study aims

The primary aim of the HEI is to generate a comprehensive biochemical roadmap detailing the human dose-response relationship between exercise and molecular activation. The HEI protocol presented in this report will first be completed with young, sedentary to normally active people, without comorbid diseases. Comprehensive blood profiling will facilitate the identification of circulating blood molecules within major biochemical molecular families (i.e., proteins, polar, moderately polar and lipid metabolites, non-coding RNAs) that are up- or down-regulated by acute bouts of exercise. Secondary aims include: 1.) the determination of the minimal intensity and duration of exercise required to induce a statistically significant change in blood concentration of exercise responsive molecules, 2.) the characterization of dose-response kinetics profiles for responsive molecules, 3.) the identification of immediate *versus* late molecular responses (i.e., molecules up- or down-regulated immediately post exercise *versus* the 60-minute recovery time point) and, 4.) the identification of sex-based differences in the exercise-dose biochemical response.

### Inclusion and exclusion criteria

Phase 1 of the HEI will study healthy, young men and women. Inclusion criteria include (1) age between 20 and 45 years, (2) self-defined white race, (3) absence of established pre-morbid conditions, (4) no active use of tobacco within the last year, and (5) structured weekly exercise that does not exceed more than 150 min of moderate intensity and/or 75 min of vigorous intensity exercise per week as recommended by contemporary physical activity guidelines [2,3,28,29]. Participants with established chronic diseases including hypertension, dyslipidemia, diabetes (type 1 and/or 2), cardiovascular disease, prior or present cancer, lung disease, autoimmune disease, or endocrine dysfunction are not eligible. Additional exclusion criteria encompass pregnancy and the presence of any musculoskeletal condition that would make exercise unsafe or impossible.

### Baseline visit

The experimental protocol will begin with the baseline screening visit during which written informed consent will be obtained prior to any subsequent study activities. Participants will complete the long version of the International Physical Activity Questionnaire (IPAQ), which quantifies physical activity performed over the previous seven days [30], provide detailed information about any routine structured exercise and routine physical activity in other domains of life, and complete a health questionnaire designed to elicit self-reported confirmation of inclusion and exclusion criteria. Subsequently, height and body mass will be measured. A resting 12-lead electrocardiogram (Cardea 20/20™, Cardiac Insight, WA, USA) and a transthoracic echocardiogram (Vivid-q™, GE Healthcare, IL, USA) will be performed to exclude occult forms of cardiac pathology associated with adverse events during exercise. Brachial artery blood pressure will be measured after cardiac assessments to ensure the acquisition of true resting values. Participants will then perform baseline spirometry inclusive of three to five forced vital capacity (FVC) manoeuvres to assess FVC and forced expiratory volume in 1 second (FEV_1_). Following spirometry, participants will perform a maximal effort limited cardiopulmonary exercise test on a motorized treadmill (Woodway Pro XL, Woodway, WI, USA) to determine peak oxygen consumption (V̇O_2peak_) as described in detail below (**see** Cardiopulmonary Exercise Testing). The V̇O_2peak_ protocol and the determination of the target intensities, as described below, will be conducted with each participant walking or running throughout the entire procedure. No walk to run transitions will be permitted. Briefly, the V̇O_2peak_ protocol will begin with a 2-min period at a slow walking (3 km/h) or slow running (~5 km/h) speed depending on participant’s desire to perform subsequent exercise sessions either walking or running. Treadmill speed will then be gradually increased until reaching the velocity that elicits a V̇O_2_ corresponding with 50% of the predicted V̇O_2peak_ derived from the Jones equations [*V**˙**O*_*2peak*_* = 4.2 - 0.032 x age* (men), *V**˙**O*_*2peak*_* = 2.6 - 0.014 x age* (women)] [31]. At this point the treadmill speed will be kept constant and the slope will be increased by 0.5% every 15 s, an incremental approach designed to optimize the accuracy of determining sub-maximal ventilatory thresholds, until volitional exhaustion. For participants who elect to walk during the V̇O_2peak_ protocol and in whom a natural walk-run transition is observed prior to reaching 50% of the predicted V̇O_2peak_, the fastest comfortable walking speed will be used for the remainder of the test and the treadmill slope will be subsequently increased as described above. Following ~ 10 min of passive recovery, the V̇O₂/work rate relationship will be determined for use in subsequent experimental visits. This experimental step will ensure that treadmill speed and slope elicit the steady state V̇O_2_ corresponding to values derived from the incremental maximal effort test. To do so, the treadmill speed and grade will be set at the levels corresponding with the V̇O2 at the four different experimental visit target intensities defined below. For each target exercise intensity, treadmill speed and slope will be gradually adjusted until reaching the steady state target V̇O_2_ for 2–4 min.

### Experimental visits

Participants will perform 10 discrete steady-state exercise sessions, each at a specified exercise dose (Fig 1). Four exercise sessions, performed on the motorized treadmill, will isolate intensity as the modifiable component of exercise dose (i.e., varying intensity at a fixed duration). Four exercise sessions, also performed on the treadmill, will isolate duration as the modifiable component of exercise dose (i.e., varying duration at a fixed intensity). Finally, two sessions will isolate the impact of exercise modality by performing testing on an up-right cycle ergometer (Excalibur Sport, Lode, Netherlands).

**Fig 1 pone.0326149.g001:**
[figure not shown]
Experimental Visit Exercise Dose Protocol. Participants will perform a total of 10 experimental visits. N = 4 will be dedicated to the manipulation of exercise duration (i.e., variable duration at a constant intensity, *blue* box), N = 4 will be dedicated to the manipulation of exercise intensity (i.e., variable intensity at a constant duration, *green* box), and N = 2 will examine the impact of differential exercise modalities (i.e., up-right cycle ergometer, *red* box).

The four pre-specified exercise intensities will be defined as the speed and incline, individualized and confirmed for each participant during the baseline visit, required to elicit a percentage of V̇O_2_ at the first ventilatory threshold (VT1) as follows: 1.) V̇O_2_ of 30% below VT1 (VT1–30%), 2.) V̇O_2_ of 15% below VT1 (VT1–15%), 3.) V̇O_2_ of VT1, and 4.) V̇O_2_ of 15% above VT1 (VT1 + 15%). These intensities were chosen to ensure that each participant would be capable of completing at least 30 min of continuous exercise at the three lowest intensities. During the VT1 + 15% visit, participants will exercise to the point of volitional exhaustion. It is anticipated that the majority of participants will reach exhaustion within 30 min under these conditions. In cases where this does not occur, the incline of the treadmill will be gradually increased to ensure that exhaustion is reached within 5 additional minutes.

The four sessions dedicated to the modification of exercise duration will be comprised of fixed intensity exercise at VT1–15% for sessions of 10, 20, 30 and 60 min. This intensity was chosen to ensure that each participant will be capable of completing the longest duration session of 60 min. To examine differential biochemical responses as a function of exercise modality, participants will complete two 30-min sessions on an up-right cycle ergometer at a cadence of 60–80 revolutions per min, each performed at a V̇O2 corresponding to −30% and −15% of treadmill-assessed VT1. Gas exchange will be monitored during the first 5–10 min to ensure that the target V̇O_2_ is reached within 5–6 min. Each session will begin with a continuous 1 W/s ramp until 80% of the target V̇O_2_ is reached, after which individualized manual adjustments will be made to achieve the final workload that correlates with the desired V̇O_2_.

A predefined sequence of exercise sessions will be applied for all participants (Fig 2). This sequence was implemented to ensure that: 1.) exercise sessions comprised of the higher exercise doses will be performed within the second half of the ten experimental visits, and that 2.) exercise sessions for which direct head-to-head comparisons are planned are not separated by more than one month (e.g., the two identical sessions performed at VT1–15% on the treadmill). To minimize the likelihood and/or impact of a physiologic training effect, consecutive visits will be separated by a minimum of 3 days and participants will abstain from any structured exercise training, above or below their pre-enrollment baseline level of habitual activity, outside of study visits for the duration of study participation.

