**Fig 2 pone.0326149.g002:**
[figure not shown]
Sequence of Experimental Visits. Following the baseline visit (*black* box), participants will be following the sequence of experimental visits shown here. Experimental sessions designed to manipulate exercise duration (*blue* boxes) will be conducted on the treadmill for: 1.) 10 min, 2.) 20 min, 3.) 30 min, and 4.) 60 min at a fixed exercise intensity of V̇O_2 _= VT1–15%. Experimental sessions designed to manipulate exercise intensity (*green* boxes) will consist of variable intensity treadmill walking/running at V̇O_2 _= 1.) VT1-30%, 2.) VT1-15%, 3.) VT1, and 4.) VT1 + 15% for a fixed duration of 30 min. Modality manipulation (*red* boxes) will include up-right cycling for 30 min at V̇O_2 _= VT1-30% and VT1-15%. * = Direct comparisons to examine differential biochemical responses to running/walking and cycling exercises. VT1 = The first ventilatory threshold.

For each experimental session, participants will report to the laboratory between 7 am and 12 pm following an overnight fast and caffeine intake abstinence. To control for circadian rhythm, all sequential experimental visits for each participant will be scheduled at the same time of the day. Upon arrival, participant body mass and body composition (BC 545, Tanita, Japan) will be recorded. Prior to exercise, an 18–22-gauge medical grade intravenous catheter will be inserted in the most easily accessible superficial peripheral vein at, or distal, to the antecubital fossa. An initial blood sample will be collected immediately prior to exercise initiation. A 5-min warm-up will then be performed at VT1–30% for all experimental sessions performed on the treadmill, or at a gradual intensity starting at 0 W and increasing up to the intensity eliciting the targeted V̇O_2_ for sessions performed on the cycle ergometer. After the 5-min warm-up, the targeted intensity will be maintained for the specific duration of the experimental sessions (i.e., 10–60 min). Immediately at exercise completion, a second blood sample will be collected. Participants will then recover for 60 min prior to the collection of a final blood sample. During the recovery period, all participants will remain seated within the facility and will remain fasted.

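### The VT1+15% session runs to exhaustion, so the intensity series does not have the fixed duration claimed for all four levels

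*Protocol article*

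**What the plan says.** The opening of Experimental visits says that four treadmill sessions "will isolate intensity as the modifiable component of exercise dose", which it explains as "varying intensity at a fixed duration". The Fig 1 caption repeats this for all four visits: "variable intensity at a constant duration". The Fig 2 caption lists the four levels by name and ends with "VT1 + 15% for a fixed duration of 30 min". The Study design section likewise describes sessions of set absolute length.

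The body text after Fig 1 says something else about the top level: "During the VT1 + 15% visit, participants will exercise to the point of volitional exhaustion". It adds: "It is anticipated that the majority of participants will reach exhaustion within 30 min under these conditions". For anyone still going, "the incline of the treadmill will be gradually increased to ensure that exhaustion is reached within 5 additional minutes". The same paragraph explains that the intensities were chosen so that each participant would be "capable of completing at least 30 min of continuous exercise at the three lowest intensities", and gives no such assurance for VT1+15%.

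**The concern.** The design claims a property that its own conduct rule removes at one of the four levels. At VT1+15% each participant sets the duration, the bout ends in exhaustion (no other session is designed to), and past 30 min the workload is no longer the nominal one.

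This matters because of what is read from the series. Statistical analyses defines the primary outcome as the intensity and duration at which a molecule differs from rest, and takes slopes over escalating intensity. Study aims seeks the minimal intensity that produces a change. Statistical analyses also expects some molecules to respond only at higher doses, and VT1+15% is the only level above VT1. A molecule that first moves there would be reported as having an intensity threshold, when duration, exhaustion or added incline could explain the change.

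**Working it through.** **1. The two rules side by side.**

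| Level | Duration per opening text and captions | Duration per text after Fig 1 |
|---|---|---|
| VT1-30%, VT1-15%, VT1 | 30 min | 30 min assured |
| VT1+15% | 30 min | to exhaustion; mostly within 30 min, otherwise up to 5 min more with rising incline |

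Both cannot hold for VT1+15%, and nothing in the article reconciles them.

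**2. Order of doses.** The Introduction defines dose as a product of intensity, duration and frequency. For one bout, take intensity relative to VT1 times minutes. At 30 min the lower levels give 0.70 × 30 = 21.0, 0.85 × 30 = 25.5 and 1.00 × 30 = 30.0. A true 30 min at VT1+15% would give 34.5. Under the exhaustion rule its dose falls below:
- VT1 if it ends before 30/1.15 = 26.1 min;
- VT1-15% before 25.5/1.15 = 22.2 min;
- VT1-30% before 21/1.15 = 18.3 min.

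The protocol gives no distribution of exhaustion times, so these are break-points, not predictions.

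**3. Leverage of the top level on the slope.** Put intensity on the axis as 70, 85, 100 and 115% of V̇O2 at VT1, with rest at 0 (an assumption). The weight w of the 115 point in the least-squares slope is its deviation from the mean divided by the sum of squares:

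| Fit | w | Slope change if the 115 response shifts by 10% of the VT1 response (100 × w × 0.10) |
|---|---|---|
| Intercept fixed at rest | 115/35350 = 0.00325 | 3.3% |
| Ten rest points | 88.57/25571.4 = 0.00346 | 3.5% |
| One rest point | 41/7970 = 0.00514 | 5.1% |
| Exercise levels only | 22.5/1125 = 0.0200 | 20% |

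The first row is closest to Statistical analyses, which makes resting concentration the participant's intercept. The last row is not the stated model and is an outer bound.

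**4. Bias from duration.** Assume response proportional to intensity × minutes. The relative slope bias is w × 115 × (T - 30)/30, with T assumed between 15 and 35 min:

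| T (min) | Intercept fixed at rest | Exercise levels only |
|---|---|---|
| 15 | -19% | -115% |
| 20 | -12% | -77% |
| 25 | -6% | -38% |
| 35 | +6% | +38% |

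The 35 min row does not count the raised incline. If duration has no effect on the molecule, every entry is 0.

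**5. Precision with three levels.** With equal independent errors, the ratio of the three-level to the four-level slope SE is:
- intercept fixed at rest: √(35350/22125) = 1.26;
- ten rest points: √(25571.4/17123.1) = 1.22;
- one rest point: √(7970/5868.75) = 1.17;
- exercise levels only: √(1125/450) = 1.58.

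**6. Can adjustment rescue the fourth level?** Fit additive intensity and duration effects to the treadmill sessions (70,30), (85,30), (100,30), (85,10), (85,20), (85,30), (85,60), with and without (115,T). In units of the error SD, the SE of the intensity slope is 0.0471 without the top session. With it, the SE is 0.0296, 0.0290, 0.0284 and 0.0286 for T = 15, 20, 30 and 35, a ratio of 1.59 to 1.66. Adding an indicator for exhaustion returns 0.0471. The precision gain therefore rests entirely on exhaustion having no effect of its own, which this design cannot test.

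**The case against.** The exhaustion rule is openly stated and looks deliberate, so no site would be misled about conduct. An exhaustive top dose is informative, the comparison of VT1+15% with rest survives, and the three lower levels are untouched. All of this stands. It limits the harm to attribution, but it does not reconcile the rule with the fixed-duration claim.

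Statistical analyses puts exercise dose on the horizontal axis. If that meant actual intensity × minutes, the duration bias in step 4 would be zero under the same response model. That is a possible reading, but such an axis would not isolate intensity either, and a threshold on it would not be an intensity threshold.

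The largest biases come from fits without rest, which the protocol does not describe. Agreed: the rest-anchored figures are the relevant ones. Two simplifications also affect them. Resting V̇O2 is not zero, and allowing for that slightly enlarges the bias. The 5 min warm-up at VT1-30% was left out; including it changes -18.7% to -16.7% at 15 min. Neither alters the conclusion.

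Finally, the choice of slope model and the capture of actual minutes could properly sit in an analysis plan or full protocol. They could, but neither would correct the article's statements or separate exhaustion from intensity.

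**Conclusion.** The article claims a fixed duration for a session that it runs to exhaustion. The claim of isolated intensity holds for three of the four levels, and there only with respect to duration, since all participants follow the same visit order. For a molecule that first responds at VT1+15%, the design shows a difference from rest but cannot say that intensity caused it.

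The contradiction itself depends on no assumption. The numerical size does: for the rest-anchored slope the bias runs from about -19% to +6% over assumed durations of 15 to 35 min if response is proportional to intensity × minutes, and is zero if duration does not matter. Any exhaustion effect is additional and cannot be estimated. This should be fixed, but it does not undermine the study as a whole.

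**What to change.** - Correct the opening of Experimental visits and both captions to describe VT1+15% as an exhaustive bout of variable duration. Align the Study design wording, and the sentence after Fig 2 that has the target intensity held for a specified time.
- Record and report actual minutes and final incline at VT1+15%.
- Keep the comparison of VT1+15% with rest, and state that a response first seen there cannot be attributed to intensity alone.
- Report the slope from the three 30 min levels beside any four-level fit, and claim an effect of intensity at fixed duration only from the former.
- Let any four-level fit use actual duration, informed by the 10 to 60 min series, and state its assumption that duration effects carry over between intensities.

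This needs no new visits or samples. The cost is precision: the three-level slope SE is 17% to 26% larger with rest anchoring the intercept, and 59% to 66% larger than in the duration-adjusted fit to all eight treadmill sessions. No threshold above VT1 could then be called purely an intensity threshold. Setting a common shorter duration at VT1+15% would remove the variability, but it would still not match the other levels' 30 min and would give up the exhaustive bout.
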